#### Randomisation

Randomisation will be completed at primary school-level and will be randomised to the intervention or control group with a fixed ratio of 2:1 schools, respectively. We will stratify by Local Authority (LA), depending on how primary feeder schools are recruited with each LA. If within one LA not enough schools are recruited to achieve a 2:1 ratio, we will ensure balance by reverting to a 1:1 ratio ensuring that at least one schools is allocated to each arm within an LA. An independent statistician at Cardiff University Centre for Trials Research (CTR) will randomise the schools after all six schools are recruited to the study to minimise drop out after randomisation. If a school withdraws before baseline data collection, they will be replaced with another randomly selected school from the same strata and retain the allocation of the school that withdrew. If a school withdraws after baseline data collection and the school has been informed of intervention allocation but none of the intervention has been delivered, the school’s baseline data collection will be reported and included in the ITT analysis. If a school withdraws after baseline data collection and they have started the intervention, then they are not replaced. The school will be followed-up as normal unless the school withdraws fully from the trial and follow-up at 12 months. Allocations will be blinded from the trial statistician and health economist. The schools will be informed of the allocation after baseline data is collected from the students. All study staff and participants will be blinded at baseline data collection.

#### Outcome measures

The outcomes that will be reported in this feasibility study are as follows:

##### Primary outcomes

Average daily minutes spent in moderate-to-vigorous physical activity (MVPA) measured using 7-day accelerometer data.

##### Secondary outcomes

Number of schools and children recruited, randomly allocated and retained at 12-month follow-up measured using recruitment data, attendance registers and interviews.Assessment of the feasibility and acceptability of the evaluation design and methods for a future full-scale trial measured using interviews and focus groups.Assessment of intervention fidelity (delivery) measured using teacher logbooks, attendance registers and session observations.Assessment of intervention acceptability to children (girls and boys), parents, school staff and role models measured through interviews and focus groupsAssessment of the feasibility of conducting an economic evaluation in a future full-scale trial using a pilot cost consequence analysis, testing pupil self-reported outcomes measures (Child Health Utility-9D (CHU-9D) [21] and EQ-5D-Y [22]).Assessment of sedentary time and time spent at different physical activity intensities within specific segments (e.g. during the club, after school or at weekends) measured using 7-day accelerometer data at baseline and 12-month follow-up.

### Progression criteria for a potential future trial

Criteria for progression to a full-scale trial will be used to inform a decision on whether and how to proceed. Each progression criterion (PC) is outlined below.The intervention is implemented with fidelity (in a manner in line with intervention theory) in at least 3 of 4 intervention schools.At least 50% of assenting children in the intervention schools attend 50% of the scheduled sessions.The process evaluation indicates the intervention is acceptable to children, parents, school staff and role models.

Progression criteria relating to obtaining data regarding completion of outcome measures will be assessed using the following progression criteria:4.At least 3 of 4 intervention schools and 1 of 2 control schools are retained throughout the study. At least 80% of children approached complete the baseline and follow-up accelerometer measures. Proceed: 80% of children complete baseline and follow-up accelerometer measure; Stop: < 50%; Review: 50–79% of children complete.5.At least 70% of recruited children who receive an accelerometer return valid data (>3 days of 600 minutes including 1 weekend day) at baseline and follow-up for the primary outcome measure. Proceed: 70% or more; Stop: <40%; Review: 40–69%

These criteria have been agreed in advance of data collection with the Trial Steering Committee (TSC). The TSC will consider the quantitative and qualitative data [23] to review and make an overall judgement on whether the intervention can be delivered with fidelity. Potential impacts of COVID-19 will be considered as well as risk of generalisability bias [24]. In line with development guidance for feasibility studies [25], the study does not aim to provide an indication of the effectiveness of the intervention; given the small, purposively selected sample, such an estimate would not be meaningful.

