#### Child recruitment and parental consent

Two main forms of data collection will be conducted at baseline and again at a 12-month follow-up:A survey of self-reported outcome measuresCollection of 7-day accelerometry data (i.e. GT3X ActiGraph accelerometer, which is a non-invasive physical activity monitoring device worn on the waistband).

Recruited primary schools will be asked to invite all girls in year 5 (ages 9–10) to participate in the study at least 2 weeks prior to the data collection date. Year 5 girls will be provided with an information sheet, fully informing them of the study. Simultaneously, all the parents/carers of year 5 girls will be sent an electronic information sheet, fully informing them of the study and giving them the opportunity to opt their child in to the study. The information sheets will detail all possible aspects of their child’s participation in the study, including the completion of a short online survey in school and accelerometer and options of withdrawal up to the point of reporting; stating that children can participate in either the survey or accelerometer or both. The information sheet will highlight that the study is about evaluating an after school programme, but which schools are allocated to receive that or act as controls is down to chance. The information sheet will clearly state that their child can still take part in the after-school programme even if they do not participate in the study.

Parents/carers will be encouraged to discuss the information with their child prior to data collection. Parental written opt-in consent will be required for children to take part in the main trial components (survey and accelerometer). Parents/carers will be asked to return the opt-in form if they are happy for their child to participate in any aspect of the study. If a parent/carer does not return an opt-in form to the school by the 2-week deadline, their child will not enter the study. The class teacher will provide daily oral reminders to the children over this period to ensure that they and their parents read the information sheet and also utilise one other usual mechanism for communication (e.g. texts or emails home).

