#### Sample size

As this study is focused on feasibility, the purpose is to provide estimates of key parameters for a future full-scale trial, rather than to power the current study to detect statistically significant differences. A total of 90 children within 6 recruited primary schools (allowing for an average of 15 girls in year 5) will allow an estimation of feasibility criteria with reasonable precision across a diverse range of context (e.g. intervention fidelity, completion of assessments, and valid primary outcome data). For girls within the intervention schools only (*n*=60), we will estimate that 50% will attend the intervention (i.e. minimum of one session) within ±12.7 percentage points using a 95% confidence interval. Similarly, for girls from all schools (*n*=90), the parameter of 70% returning valid primary outcome data can be estimated within ±9.5%, and 80% will complete baseline/follow-up to within ±8.3%.

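### Progression criterion 4 counts accelerometer completion out of girls approached, so its result cannot exceed the opt-in rate even if no recruited girl is lost

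*Protocol article*

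**What the plan says.** All references are to the Protocol article. Progression criterion 4 (PC4) has two clauses. The school clause reads "At least 3 of 4 intervention schools and 1 of 2 control schools are retained throughout the study". The child clause reads "At least 80% of children approached complete the baseline and follow-up accelerometer measures". The bands that follow are "Proceed: 80% of children complete baseline and follow-up accelerometer measure; Stop: < 50" per cent, with Review in between; that line no longer says approached.

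The neighbouring criteria name other groups. PC2 reads "At least 50% of assenting children in the intervention schools attend 50% of the scheduled sessions", and PC5 begins "At least 70% of recruited children who receive an accelerometer return valid data".

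On who is approached, Child recruitment and parental consent says "Recruited primary schools will be asked to invite all girls in year 5 (ages 9–10) to participate in the study". The same section says "Parental written opt-in consent will be required for children to take part in the main trial components (survey and accelerometer"). A girl whose form is not returned by the deadline stays out of the study, and a girl may do the survey without the accelerometer. Under Activity monitor, monitors go to opted-in children.

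The Sample size section states that "80% will complete baseline/follow-up to within ±8.3" percentage points, on n=90. The abstract describes about 90 girls as the number to be recruited. Classroom report lists counts of opt-ins, absentees and pupil opt-outs. Study objectives refers to six progression criteria; five are numbered.

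**The concern.** PC4 stands among the criteria on completion of outcome measures, so it should show whether the accelerometer data can be collected at both waves. If its denominator is every girl invited, each girl whose parent does not opt in counts as a failure to complete a measurement she was never offered. So does a girl who joins the survey only.

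Low consent and poor wear or follow-up then produce the same traffic light, although they call for different remedies in a full trial. If approached was meant more narrowly, the text does not say so, and two analysts could report different bands from the same data. What is at stake is a criterion with a Stop line, agreed in advance with the Trial Steering Committee (TSC), on whether the primary outcome can be collected.

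**Working it through.** **1. The plan's own figures.** The half-width is 1.96 × √(p(1−p)/n).
- p = 0.80, n = 90: 1.96 × √(0.16/90) = 8.26 points (stated 8.3).
- p = 0.70, n = 90: 1.96 × √(0.21/90) = 9.47 points (stated 9.5).
- p = 0.50, n = 60: 1.96 × √(0.25/60) = 12.65 points (stated 12.7).

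All three reproduce, so the 80% was planned on 90 girls.

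**2. What PC4 measures on its plain reading.** Let s be the share of approached girls in schools that stay, c the share of approached girls who are opted in and assent to the accelerometer, and r the share of those girls in retained schools who complete both waves. Taking c as equal across schools, PC4 rate = s × c × r. With s = r = 1 the rate is c, so opt-in is the ceiling.

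**3. Size.** The documents give no value for c, so these values are assumptions. All schools are retained (s = 1), and the r needed for Proceed is 0.80/c.

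| Assumed opt-in c | Ceiling with no attrition | Band at the ceiling | r needed for 80% |
|---|---|---|---|
| 100% | 100% | Proceed | 80.0% |
| 90% | 90% | Proceed | 88.9% |
| 80% | 80% | Proceed | 100% |
| 70% | 70% | Review | 114%, impossible |
| 45% | 45% | Stop | 178%, impossible |

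**4. In girls.** If 90 are recruited and all complete, Proceed needs 90/N ≥ 0.80, so N ≤ 112.5, that is at most 112 approached (90/112 = 80.4%; 90/113 = 79.6%). Above 90/0.50 = 180 approached, the result is Stop.

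**5. Denominators side by side.** The Sample size section uses n=90 both for the 70% of PC5 and for the 80% of PC4. PC5's group has been recruited and given a monitor; PC4's has only been approached. Both can number 90 only if c = 100%. With opted-in girls as denominator, perfect retention gives 90/90 = 100%, and the 80% line is 72 of 90, which fits the precision statement.

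**6. The school clause (secondary).** Its floor is 3 + 1 = 4 of 6 schools. At the planned average of 15 girls, at most 4 × 15 = 60 of 90 girls (66.7%) can complete, under either denominator. With five schools the cap is 75/90 = 83.3%, and 72 of the remaining 75 (96%) must complete. At the four-school floor with an assumed 70% opt-in, the approached rate is at most 0.667 × 0.70 = 46.7%, which is Stop although the school clause is met. With unequal schools, 80% stays attainable if the two lost schools hold no more than 18 of the 90 girls.

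**The case against.** The strongest reply is that approached is undefined and could mean opted-in girls asked to wear the monitor. The band line says only children, and PC4 is grouped with completion of outcome measures. Likewise, the Sample size section speaks of 90 children within six recruited schools and of an average of 15 girls in Year 5, which could be the whole Year 5 roll. Approached and n=90 would then coincide. This stands as a possible reading, and under it the fault is ambiguity. But the invitation to all Year 5 girls is the only approach described, the abstract calls the 90 recruited, and PC5 uses the same 90 for girls already holding monitors.

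It can also be said that the criteria only inform the decision, that the TSC considers quantitative and qualitative data, and that missing 80% leads first to Review. That is right, and it limits the consequence.

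A reader might infer that the school clause contradicts the child clause. It does not: both are minimums, and the school one is merely looser. The 67% cap also needs schools of roughly equal size, while School recruitment and retention selects for variation in size.

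**Conclusion.** The denominator of PC4 should be fixed. On its plain reading the criterion cannot exceed the accelerometer opt-in rate: with no attrition, opt-in below 80% rules out Proceed and opt-in below 50% forces Stop. The wording also departs from PC2, PC5, PC4's own band line and the n=90 basis of the precision figure. This rests on reading approached as invited; on the narrower reading, an undefined term remains.

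Three stronger conclusions are not supported.
- That Proceed is out of reach in this trial: no opt-in rate is given. The formative study's 46 of 64 girls (72%) is programme attendance, and the protocol lets a girl attend the programme without joining the study, so it does not estimate opt-in.
- That a miss ends progression: the criteria inform a judgement.
- That six against five criteria shows one was lost: counting PC4's two clauses separately gives six, so this is editorial.

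The school clause is a secondary point. At about 15 girls per school, meeting only its floor would usually not permit Proceed.

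**What to change.** State the child criterion as: of girls opted in and assenting to the accelerometer at baseline, in all randomised schools, at least 80% complete both waves. Keep the 80% and 50% lines.

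Girls in withdrawn schools should stay in the denominator. Restricting it to retained schools would hide school-level attrition: with two of six equal schools lost and 48 of the remaining 60 girls completing, it would show 48/60 = 80%, against 48/90 = 53% overall. A retained-schools figure may be reported beside the main one.

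List school retention as its own criterion, which brings the numbering to six. Report opt-in (opted in / invited) separately as the recruitment outcome, and add the number of girls invited to the classroom report, whose listed counts do not include it.

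The cost is a change of wording, one extra count per school and TSC confirmation before completion results are seen. The downside is that consent no longer moves this traffic light, so the opt-in rate must be read beside it.

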### Data collection

In the current climate, many (if not all) schools will not allow non-staff members access to their premises. Therefore, minimal face-to-face data collection methods have been included within the current project. Data collections will be mainly teacher-led (with virtual attendance by an online researcher where requested) and an electronic survey method offered. Where data collection materials need to be provided to the school (e.g. activity monitors and paper surveys), we have developed a safe contactless delivery approach.

Data collection will be overseen by the class teacher in normal class time. Teachers will be provided with a study introduction sheet which contains a script that they will read out to their pupils, along with some ‘dos’ and ‘don’ts’.

### Classroom report

Using a standardised template, the teacher will be asked to provide count information on the number of parental opt-ins, number of absentees and the number of pupil opt-outs (via hard copy or electronic).

### Survey

The survey will be made available in English and Welsh and will be self-completed by pupils within the classroom under teacher supervision during school hours. Data collection will be facilitated by electronic data capture using a bespoke Qualtrics database, and paper copies of the survey will also be made available. Schools will be asked when signing up to the study if they would prefer electronic or pen and paper format. Each child opted into the study by their parents/carers will be allocated a unique Participant ID ahead of data collection, ensuring all participant data are pseudonymised.

The survey will collect data on demographics (age, gender and ethnicity), self-reported physical activity (Physical Activity Questionnaire for Older Children (PAQ-C scale)) [26], psychosocial outcomes (activity-based perceptions of autonomy, relatedness, competence and enjoyment), current after-school sport or physical activity club attendance (school and community) and health-related quality of life ((CHU-9D [21] and the EQ-5D-Y) [22]). Three schools will complete the EQ-5D-Y, and three schools the CHU-9D to reduce burden on pupils completing the questionnaires, whilst retaining the ability to answer feasibility questions. All questions will be closed response, with an ‘I do not want to answer’ option provided throughout. For electronic survey collections, the software will enable partial survey completions to be captured.

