**Methods:**

This study is a feasibility cluster randomised controlled trial, with embedded process evaluation and health economic evaluation. Approximately 90 Year 5 (i.e. 9–10-year-old) girls will be recruited across six primary schools in Mid-South Wales. Participating schools will be allocated to the programme: control on a 2:1 basis; four intervention schools will run the CHARMING Programme and two will continue with usual practice. A survey and accelerometer will be administered at baseline and repeated at 12 months. Interviews and focus groups will be conducted post-intervention delivery. The primary aim is to assess feasibility of a future randomised trial via the recruitment of schools, participants and role models; randomisation; retention; reach; data collection completion rates; programme adherence; and programme fidelity, views on intervention acceptability and programme barriers and facilitators. Secondary aims are to evaluate established physical activity outcome measures for children plus additional health economic outcomes for inclusion in a future full-scale trial.

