#### Economic analysis

A Health Economics Analysis Plan (HEAP) in accordance with the main statistical analysis plan will set out the objectives and methods for data collection and analysis of the health economics findings. A pilot cost consequence analysis will test the feasibility of conducting an economic evaluation in a future full-scale trial. Response rates and level of completion of the economic measures of EQ-5D-Y, CHU-9D at baseline and 12-month follow-up will be reported using descriptive statistics taking account of clustering. Ceiling effects in the health-related quality of life measures EQ-5D-Y and CHU-9D will be assessed.

During teacher interviews at intervention schools, questions will be added to explore if it is feasible to identify and measure the resources required to deliver the intervention to estimate a cost per programme and per participant, using micro-costing methodology used successfully in previous studies [29, 30].

Topic Guide questions will inquire about time taken to set up and delivery the intervention, such as time to recruit role models, session planning, and liaising with local organisations to deliver sessions. We will liaise with teachers responsible for intervention delivery to gather this information, including information on teacher salary band.

Teacher costs will be sourced from the National Union of Teachers (NUT) [31] pay structure for qualified classroom teachers in Wales. School based costs will be collected from a Local Education Authority perspective, accounting for on-costs (e.g. national insurance and pension costs), and using the cost year 2020–2021.

Parents taking part in the one-to-one interviews will be asked about their willingness to answer questions regarding their child’s use of primary care such as the GP, nurse, and hospital services, and whether there are other services they feel are important to include. Whether parents would be willing to complete a questionnaire at study time points (e.g. at baseline and follow up) and what format they would prefer the questionnaire to be in (e.g. paper or online). These questions would help inform the development of a Client Service Receipt Inventory (CSRI) as part of a cost-effectiveness analysis in a subsequent definitive randomised controlled trial.

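### Giving EQ-5D-Y and CHU-9D to different whole schools confounds instrument with school and weakens the evidence on which measure to carry forward

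*Protocol article*

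**What the plan says.** The Survey section assigns the two health-related quality-of-life instruments by school: "Three schools will complete the EQ-5D-Y, and three schools the CHU-9D to reduce burden on pupils completing the questionnaires", and adds that this is done "whilst retaining the ability to answer feasibility questions". The same section says that schools choose between electronic and paper format at sign-up, that pupils complete the survey under their teacher's supervision, and that each opted-in child receives a unique Participant ID before data collection.

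Under School recruitment and retention, the feeder primary schools are selected purposively to differ in free-school-meal eligibility, location and size.

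On allocation, the Abstract says that "four intervention schools will run the CHARMING Programme and two will continue with usual practice". The Randomisation section has schools "randomised to the intervention or control group with a fixed ratio of 2:1 schools, respectively". If a Local Authority supplies too few schools for that ratio, "we will ensure balance by reverting to a 1:1 ratio". Study staff are blinded at baseline data collection.

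The Economic analysis section plans descriptive reporting of response and completion for both instruments at baseline and 12 months, taking account of clustering, and says "Ceiling effects in the health-related quality of life measures EQ-5D-Y and CHU-9D will be assessed". The Abstract gives evaluation of health economic outcomes for inclusion in a full-scale trial as a secondary aim. The Discussion says that the findings will inform which outcome measures are chosen.

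**The concern.** Two candidate measures are fielded side by side, and the study is meant to help decide which outcome measures go forward. A reader of the results will naturally compare the completion and ceiling figures for EQ-5D-Y with those for CHU-9D. Under the stated rule, those figures come from two different sets of three schools, and the schools were deliberately chosen to be unlike one another. A lower completion rate or a higher ceiling on one instrument could reflect the instrument, the teacher, the survey format, or the health and background of the girls in those three schools. Allowing for clustering widens the intervals but does not remove the confounding.

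The stated reason for the split is pupil burden. That requires each child to complete only one instrument. It does not require every child in a school to complete the same one.

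A lesser matter is that the article does not link the three/three instrument split to the four/two split by arm, so one instrument could end up with no control school.

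**Working it through.** **Inputs.** From the Sample size section: 90 girls, 6 schools, an average of 15 per school, hence 3 × 15 = 45 girls per instrument. From the Abstract: 4 intervention and 2 control schools. The 80% completion rate is borrowed from the Sample size section as a working value. No intraclass correlation (ICC) for completion is given, so 0.01, 0.05 and 0.10 are assumptions.

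**The plan's own precision figures.** The half-width 1.96 × √[p(1 − p)/n] gives:
- p = 0.50, n = 60: 12.65 points, matching "within ±12.7 percentage points using a 95% confidence interval"
- p = 0.70, n = 90: 9.47, matching the stated 9.5
- p = 0.80, n = 90: 8.26, matching the stated 8.3

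These reproduce without a clustering term. None is specific to an instrument.

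**One instrument on its own (p = 0.80, n = 45, by school).** The half-width is 1.96 × √(0.16/45) = 11.7 points ignoring clustering. Multiplying by the square root of the design effect, 1 + (15 − 1) × ICC, gives 11.7 × √1.7 = 15.2 at ICC 0.05 and 11.7 × √2.4 = 18.1 at ICC 0.10.

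**Difference between instruments (p = 0.80, 45 girls each).**
- By whole school: 1.96 × √{2 × 0.16 × [1 + 14 × ICC]/45}
- Split within school: 1.96 × √{2 × 0.16 × (1 − ICC)/45}, because a school effect common to both instruments cancels

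| Assumed ICC | Design effect, by school | By school | Within school |
|---|---|---|---|
| 0.01 | 1.14 | ±17.6 | ±16.4 |
| 0.05 | 1.70 | ±21.6 | ±16.1 |
| 0.10 | 2.40 | ±25.6 | ±15.7 |

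The entry 21.6 is 21.55 before rounding. Both columns use the normal approximation, so they compare like with like. With six schools in two groups, a t multiplier on 4 degrees of freedom (2.776) would widen the by-school figure at ICC 0.05 to 21.55 × 2.776/1.96 = 30.5. That is not set against the within-school figures, which use 1.96.

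**Control schools per instrument.** There are C(6,3) = 20 ways to choose the three EQ-5D-Y schools. With two control schools, C(2,1) × C(4,2) = 2 × 6 = 12 of these place one control school in each instrument group. The other 20 − 12 = 8 (40%) put both control schools on one instrument and none on the other. If the 1:1 fallback produced three schools per arm, only 2 of 20 (10%) would leave an instrument without a control school.

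In the 12 balanced cases each instrument rests on a single control school of about 15 girls. Progression criterion 4 tolerates the loss of one of the two control schools, and in those cases that loss would leave one instrument with no control data at 12 months.

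**The case against.** The strongest reply is that the plan promises no comparison. Response, completion and ceiling are to be described for each measure, and three schools suffice to see whether 9–10-year-olds can complete an instrument and whether scores pile up at the top. That stands. A reader might infer that the choice of utility measure would rest on a three-versus-three school contrast, but the document does not say so: its references to choosing or including measures are general, and no head-to-head analysis is specified.

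A reader might also infer that one instrument will lack control data and that the economic work would be undermined. Neither follows.
- The 40% assumes that instruments are assigned without regard to arm. The article does not say how the three schools are chosen. It refers methods of health-economic data collection to a Health Economics Analysis Plan that is not shown, and the independent statistician could place one control school in each group.
- The consequence is limited. Schools learn their allocation only after baseline, so baseline completion and ceiling should not depend on arm. The article disclaims any estimate of effectiveness, and the cost-consequence analysis is a test of feasibility. What could be lost is mainly a by-arm description of one instrument at 12 months.

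The alternative design also has a price. Data collection is mainly teacher-led with little face-to-face contact, and the survey already varies by language and format. A second version in each class adds handling and, on paper, some risk that a child receives the wrong one. This is a fair cost but a modest one.

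Finally, ±16 points is still wide, so the within-school split would not settle a small difference. Its main benefit is to remove the confounding; the gain in precision is secondary and nearly vanishes at an ICC of 0.01.

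**Conclusion.** The point holds as a worthwhile and inexpensive design improvement, not as a fatal flaw. The confounding follows directly from the stated rule and needs no assumption. An analysis plan that keeps school-level assignment could not undo it, whatever it says about clustering or balance by arm.

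The gain in precision from a within-school split is about 1, 5 and 10 points of half-width at ICCs of 0.01, 0.05 and 0.10. It depends on those assumed ICCs, on 80% completion, on all 45 girls per instrument being available, and on school effects acting alike on both instruments.

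The missing-control risk is secondary and conditional: 40% under a 4:2 split with assignment that ignores arm, 10% under 3:3, and possibly nil at baseline if the unseen plan balances instruments by arm.

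**What to change.** Randomise the instrument by pupil within each school, using a list balanced within school and tied to the Participant ID issued before data collection. Implement it as a branch in the Qualtrics survey or as paper versions pre-labelled with the ID, and give each child the same instrument at 12 months. Each instrument then has about 45 girls across all six schools, roughly 30 intervention and 15 control, and the chance of an instrument with no control school at baseline falls to zero. Burden per child is unchanged.

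The cost is survey set-up, one or two sentences in the protocol, teachers supervising two versions in a class, and matching paper versions to IDs at both time points.

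Placing one control school in each instrument group would be a partial remedy. It removes the baseline control-data risk but leaves the confounding and the reliance on one control school per instrument.

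If baseline surveys have already been completed by school, keep each child's instrument for follow-up, report each measure separately and by school, and state that differences between the instruments cannot be separated from differences between schools.
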